**Conclusions:**

By collecting a wide range of data before, during, and after treatment in a large group of patients with IBS and diverse bowel habits, we will gain new insights into the predictors of response to treatment. That information can, in the future, be used to personalize treatment for the patient, based on the individual’s phenotype and IBS symptoms. In addition, the long-term effects of 2 different dietary treatments will be evaluated regarding their impact on gut microbiota and clinical laboratory tests and to ensure that they are safe, effective, and applicable for patients with IBS.

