### Research Objectives and Hypotheses

The aim of this study is to compare the effectiveness of three different treatment options for patients with IBS: a low-carbohydrate diet (LCD), a diet combining low FODMAP and traditional dietary advice (LFTD), and optimized medical treatment (OMT). The trial has been registered at ClinicalTrials.gov NCT02970591.

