### Sample Size

The power calculation is based on the primary outcome, where the expected response rate is set to 40% (LCD), 65% (LFTD), and 40% (OMT) in the treatment arms. With 80% power to detect differences between groups, and α=.05, 83 patients will be needed in each group. To account for a 15% dropout rate, we will assign 100 patients to each treatment arm.

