#### Secondary Outcome

The secondary outcomes are as follows:

A more conservative cutoff limit in IBS-SSS reduction will be tested, both with a score reduction of ≥100 and ≥50% of the initial IBS-SSS score. Proportions between treatment arms will be compared using chi-square tests.The absolute and percent change in IBS-SSS and GSRS-IBS from randomization visit to the end of intervention period will be analyzed using paired-sample *t* tests within groups and analysis of variance (ANOVA) between groups.Compliance to treatment in relation to treatment outcome will be analyzed using linear regression, with the measure of compliance as the independent variable and IBS-SSS as the dependent variable.Predictors of response to treatment (demographics questionnaire data, microbiota, metabolites, and immunology) will be analyzed using logistic regression, with *responders* and *nonresponders* as the binary outcome variable.Determinants of GI symptoms will be assessed using linear regression, with GSRS-IBS and IBS-SSS as dependent variables.Maintained adherence to dietary intervention will be assessed using food diaries at 3- and 6-month follow-ups, and differences in nutrient intake will be compared between the 2 diets using unpaired-sample *t* tests. Predictors for long-term adherence to diet will be analyzed using logistic regression, with *adherence* and *nonadherence* as binary outcome variables.Changes in extraintestinal symptoms, QoL, work productivity, and psychological factors in relation to treatment will be analyzed using ANOVA for continuous variables and chi-square tests for categorical variables.

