### Statistical Methods

Normally distributed variables will be presented as mean (SD) and nonnormally distributed variables as median (range). Differences in means between the 3 intervention groups will be analyzed with ANOVA, using Bonferroni corrections for multiple testing. For the main outcome, that is, to compare the proportion of responders in each treatment group, chi-square tests will be applied. For absolute change in IBS-SSS, the percentage change will be calculated and analyzed with paired *t* tests within groups (baseline vs end of intervention) and using ANOVA for comparisons between groups. The proportion of patients with ≥50% decrease in IBS-SSS will be compared using chi-square test between the groups. For comparing the changes at multiple time points (during follow-up), mixed model analyses will be used.

Logistic regression will be applied to evaluate predictors of response for the various treatments (binary outcome responders or nonresponders), and the determinants of GI symptoms (IBS-SSS, as a continuous variable) will be assessed using bivariate and multivariable linear regression analyses. Furthermore, multivariate analyses and bioinformatics will be applied to metabolomics, microbiota, and immunological markers.

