## Discussion

### Principal Findings

The Carbohydrates in Irritable Bowel Syndrome (CARIBS) study is a large, randomized controlled study of high quality, which is of importance when results are interpreted for implementation in the treatment of patients with IBS. As large quantities of data will be collected, exploring both the efficacy of the intervention during a 4-week period, as well as the effectiveness during follow-up, this study will bring new insights into the management of IBS symptoms.

As we do not know the long-term effects of maintaining an LCD or an LFTD, both of which are exclusion diets, we will carefully monitor the 2 groups receiving dietary treatment for 6 months. Studies have demonstrated that a lack of fermentable carbohydrates in the diet can alter the composition and diversity of the gut microbiota, which could potentially lead to adverse health outcomes in the long run [29]. In addition, studies have shown that restrictive diets can affect the total energy intake, which could lead to unwanted weight loss and a lack of nutrients [30,31]. Therefore, we have added a 6-month follow-up to the study protocol to study the effects on nutrient intake as well as the gut microbiota composition.

We anticipate that this randomized controlled trial will provide a better understanding of the predictors of response to treatment and how best to tailor treatments for patients with IBS with different symptomatology.

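### The stated predictor analysis contains no test of whether a factor's effect differs between treatments, so it does not support the tailoring conclusions attached to it

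*Protocol article*

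**What the plan says.** The predictor analysis is stated twice in the protocol article. Statistical Methods: "Logistic regression will be applied to evaluate predictors of response for the various treatments (binary outcome responders or nonresponders". Secondary Outcome: "Predictors of response to treatment (demographics questionnaire data, microbiota, metabolites, and immunology) will be analyzed using logistic regression", with responder status as the binary outcome. The sentence in Statistical Methods suggests a model per arm. The one in Secondary Outcome does not say whether the models are per arm or pooled. Neither place, nor any other, names a treatment-by-predictor term or a comparison of predictor effects between arms.

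The use to be made of the predictors is also stated. According to the abstract's Conclusions, the information on predictors "can, in the future, be used to personalize treatment for the patient". The Discussion (Principal Findings) anticipates "a better understanding of the predictors of response to treatment and how best to tailor treatments for patients with IBS with different symptomatology". The Background section argues in the same direction: IBS is heterogeneous, personalized options are needed, and a large randomized trial with a close look at predictors is therefore warranted.

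In the hierarchy of aims, Research Objectives and Hypotheses puts the comparison of effectiveness first: "The aim of this study is to compare the effectiveness of three different treatment options for patients with IBS". Finding pretreatment predictors is the fourth of five specific aims, and its analysis is listed under secondary outcomes.

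**The concern.** A factor associated with response within one arm may be purely prognostic: patients who have it may improve more on all three treatments. Such a factor says who tends to get better, not which treatment to give. Choosing between treatments needs evidence that the difference in response between arms changes with the factor, which is a treatment-by-factor interaction. Randomization to three arms makes that estimable, but the stated method does not ask for it.

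What is at stake is how the secondary results are read. If three sets of within-arm results are reported side by side with no formal contrast, a factor that is significant in one arm and not in another is easily taken as specific to that treatment. With this arm size, such patterns arise often by chance.

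**Working it through.** **The plan's own figures.** The protocol gives no figure for the predictor analysis, so the check borrows from Sample Size: "the expected response rate is set to 40% (LCD), 65% (LFTD), and 40% (OMT) in the treatment arms", with 83 needed per group and 100 assigned to allow for 15% dropout.
- The usual formula for two proportions is n = [z(α/2)·√(2p̄q̄) + z(β)·√(p₁q₁ + p₂q₂)]² / (p₁ − p₂)².
- At two-sided 0.05 it gives [1.960×0.706 + 0.842×0.684]² / 0.25² = 61.4, so 62. At 0.05/3 it gives [2.394×0.706 + 0.842×0.684]² / 0.25² = 82.2, so 83. The stated 83 therefore fits a multiplicity-adjusted α. This has no bearing on the present point.
- Dropout: 83/0.85 = 97.6, rounded up to 100. Evaluable per arm: 100 × 0.85 = 85.

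**Assumptions not in the document.** One binary baseline factor with 50% prevalence (42.5 patients per level per arm), the same odds ratio (OR) in every arm, and a two-sided 0.05 test in each arm. A common OR means no interaction on the logistic scale, so any apparent treatment-specific predictor is false.

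**Step 1: power within one arm at OR 2.** Choose response probabilities p₀ and p₁ for the two factor levels so that the arm mean equals the planned rate. With SE² = 1/(42.5·p₀q₀) + 1/(42.5·p₁q₁):
- 40% arms: p₀ = 0.318, p₁ = 0.482, SE = 0.450, z = 0.693/0.450 = 1.54, power 0.337.
- 65% arm: p₀ = 0.572, p₁ = 0.728, SE = 0.464, z = 0.693/0.464 = 1.50, power 0.321.

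**Step 2: chance of a split verdict.** Let a be the power in each 40% arm and b the power in the 65% arm. The arms are independent, so P(significant in some but not all arms) = 1 − a²b − (1−a)²(1−b) = 1 − 0.337²×0.321 − 0.663²×0.679 = 0.665.

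**Step 3: simulation.** 40,000 trials for each OR, Wald test in each arm, and a 2-df test of equal log odds ratios across the three arms as the interaction test:

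| Common OR | Significant in some but not all arms | All three arms | Interaction test falsely positive |
|---|---|---|---|
| 1.5 | 37% | 0.3% | 4.9% |
| 2 | 66% | 4% | 4.9% |
| 2.5 | 75% | 14% | 4.9% |
| 3 | 67% | 29% | 4.8% |
| 4 | 38% | 62% | 4.8% |

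The formula in Step 2 gives 38%, 67%, 75%, 68% and 44% for the same rows. It agrees closely except at OR 4, where the normal approximation understates power within each arm. The split is most frequent when power per arm is near one half, and falls off on both sides.

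**Step 4: the pooled alternative.** A single model without arm×factor estimates one OR for all arms. Its result has the same form whether or not the factor acts differently by treatment, so it holds no test of the difference.

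**Step 5: what an interaction test can detect.** Compare the LFTD arm (mean 65%) with the OMT arm (40%), with no effect of the factor in OMT. For a ratio of odds ratios of 2: SE² = 0.215 + 2/(42.5×0.24) = 0.411, SE = 0.641, z = 1.08, power 19%. For a ratio of 3: SE = 0.651, z = 1.69, power 39%. The LFTD-only model has 32% and 63% power for the same effects, but it answers a different question.

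**The case against.** Several objections carry weight.

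- **Aim.** A reader might infer that showing who does better on which treatment is the trial's main purpose. The document does not say so. The overall aim is to compare effectiveness. The fourth specific aim and the fifth secondary hypothesis speak of predicting response or outcome, which logistic regression of responder status does answer. The tailoring language stands in the abstract, Background and Discussion, and it is hedged.
- **What the models can do.** A reader might also infer that the planned models could never reveal differential effects. That is too strong. Separate logistic models with the same covariates in every arm are equivalent to one fully interacted model, and their coefficients could be compared. What is absent is a plan to compare them.
- **Model form.** The per-arm reading is inferred from one phrase, and the article does not list model terms. It is a condensed account, and a fuller plan may contain an interaction.
- **Harm.** Nowhere does the protocol say that lists of significant factors or P values will be compared across arms. The split-verdict percentages measure harm only if someone reads the results that way.

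These points limit the wording but do not remove the point. The article states both the method and the conclusion it is to serve. Whether the models are per arm or pooled, the method as stated includes no step that leads to that conclusion. This is a mismatch between two things the article does say, not a complaint about detail left out.

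**Conclusion.** The point holds as a mismatch between the stated predictor analysis and the tailoring statements in the abstract's Conclusions, the Background and the Discussion. Under either reading of the model, the analysis as written does not test whether a factor changes the difference between treatments.

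The risk of a misleading pattern is material over a plausible range: a purely prognostic factor gives a split verdict in 37% to 75% of trials for odds ratios from 1.5 to 4, against about 5% false positives for an interaction test. These figures rest on the assumed prevalence, common odds ratio and single factor, and on 85 evaluable patients per arm.

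The primary comparison of responder proportions is untouched. This is a secondary, exploratory analysis, and the point is worth correcting on that footing.

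**What to change.** For the predictor aim, state one logistic model on all randomized patients with arm, baseline factor and arm×factor, keeping continuous factors continuous, and label it exploratory. Call a factor a predictor for choosing treatment only on the strength of the interaction, and report it as the difference in response between arms across values of the factor. Describe associations within an arm as prognostic.

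If this is not wanted, limit the statements in the abstract's Conclusions and the Discussion to factors associated with response within an arm. If a fuller plan already contains the interaction, a sentence in Statistical Methods saying so is enough.

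The cost is wording and analysis time only; no design or data collection changes. The drawback is low power: about 19% and 39% for ratios of odds ratios of 2 and 3 under the assumptions above. Few treatment-selecting predictors will be claimed, and a nonsignificant interaction must not be read as evidence that a factor acts alike in all arms.

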## Discussion

### Principal Findings

The Carbohydrates in Irritable Bowel Syndrome (CARIBS) study is a large, randomized controlled study of high quality, which is of importance when results are interpreted for implementation in the treatment of patients with IBS. As large quantities of data will be collected, exploring both the efficacy of the intervention during a 4-week period, as well as the effectiveness during follow-up, this study will bring new insights into the management of IBS symptoms.

As we do not know the long-term effects of maintaining an LCD or an LFTD, both of which are exclusion diets, we will carefully monitor the 2 groups receiving dietary treatment for 6 months. Studies have demonstrated that a lack of fermentable carbohydrates in the diet can alter the composition and diversity of the gut microbiota, which could potentially lead to adverse health outcomes in the long run [29]. In addition, studies have shown that restrictive diets can affect the total energy intake, which could lead to unwanted weight loss and a lack of nutrients [30,31]. Therefore, we have added a 6-month follow-up to the study protocol to study the effects on nutrient intake as well as the gut microbiota composition.

We anticipate that this randomized controlled trial will provide a better understanding of the predictors of response to treatment and how best to tailor treatments for patients with IBS with different symptomatology.

## Abbreviations

ANOVA: analysis of variance
BSF: Bristol stool form
CARIBS: Carbohydrates in Irritable Bowel Syndrome
FODMAP: fermentable oligosaccharide, disaccharide, monosaccharide, and polyol
GI: gastrointestinal
GSRS-IBS: Gastrointestinal Symptom Rating Scale–IBS
IBS: irritable bowel syndrome
IBS-QoL: irritable bowel syndrome–quality of life
IBS-SSS: IBS Severity Scoring System
LCD: low-carbohydrate diet
LFTD: low FODMAP and traditional dietary advice
NICE: National Institute for Health and Care Excellence
OMT: optimized medical treatment
OPLS-DA: orthogonal projections to latent structures discriminant analysis
OPLS-EP: orthogonal projections to latent structures with effect projection
PHQ: Patient Health Questionnaire
QoL: quality of life
